#### Quality of life

The Cystic Fibrosis Questionnaire on Quality of Life, which was translated and validated into Portuguese in 2006, will be used for the quality-of-life evaluation. Four versions of the questionnaire exist, and these are adapted to different age groups: 6 to 11 years old (35 questions), 12 and 13 years old (35 questions), 14 years old or older (50 questions), and parents of children between 6 and 11 years old (44 questions). For children between 6 and 11 years old, the questionnaire will be supplemented with special cards for the child’s responses. The questionnaire addresses the following domains: physical health, body image, digestion, respiration, emotional state, social abilities, nutrition, treatment, vitality, health, social role, and weight. The scores for each domain range from 0 to 100, with a good quality-of-life scoring at or above 50 [53].

#### CF exacerbations

In order to evaluate CF exacerbations, which normally require an increase and/or modification of antibiotics, the following Fuchs criteria adapted by the European Consensus Group will be used [32]: change in volume and/or color of secretion; increases in coughing, fatigue or lethargy; anorexia or weight loss; decrease in lung function of 10% or more as observed on X-ray; and increased dyspnea. The individual must present at least two of these criteria for an exacerbation to be confirmed.

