**Methods:**

This study will be a two-arm, prospectively registered, randomized controlled trial with blind assessors and twenty 6- to 18-year-old individuals with cystic fibrosis (CF) from two different Brazilian states. People with CF will be randomly allocated to either the experimental or control group using block randomization, stratified by puberty stage,. Participants from both groups will receive an educational intervention and will be asked to continue their usual daily treatment for the full duration of the study. Those in the experimental group will perform AIT on a cycle ergometer at home three times a week, for 8 consecutive weeks. The sample characterization will include an assessment of puberty stage, socioeconomic status, dyspnea, and anthropometry. The primary outcome will be the change in glucose tolerance, while the secondary outcomes will include lung function, exercise tolerance, respiratory muscle strength, quality of life, and CF exacerbations. All outcomes will be assessed at baseline, week 9, and week 17.

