### Sample size calculation

The sample size calculation was performed by GPower 3.1 software, with a power of 80% and an α of 0.05 being adopted. This procedure was based on the study by Beaudoin et al. (2017) [21], which presents a similar design regarding the same number of groups and the use of exercise as an intervention, although it was developed for adults with CF. In this study, the variable area under the glucose curve after the concurrent exercise program presented values of 34.47 ± 4.23 in the experimental group (EG) and 40.20 ± 11.96 in the control group (CG), with an effect size of 0.30. Based on these parameters, the sample size calculation was 20 participants, with 10 in each group.

The children and the adolescents who discontinue participation in the study will be invited to participate in the assessments 8 weeks after starting treatment, as well as 8 weeks after the end of the intervention. Thus, all individuals will be included in the intention-to-treat analysis.

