### Secondary outcomes

#### Lung function

Spirometry will be conducted using a KoKo DigiDoser spirometer (Longmonth, USA), as per the recommendations of the American Thoracic Society (ATS) and the European Respiratory Society (ERS) [43]. Manual calibration of the equipment will be conducted during the examination, following the instructions of the manufacturer and using a 3-L syringe (Vitalograph, Buckingham, England). A disposable mouthpiece and a bactericidal filter (MicroGard 36-MGF1100) will be attached to the apparatus. These parts will be replaced and discarded after each participant use.

A mouthpiece and nasal clip will be used to avoid leaks, and the individual will be instructed on their participation in the examination. The forced vital capacity (FVC), forced expiratory volume in the first second (FEV_1_), Tiffeneau index (FEV_1_/FVC), and forced expiratory flow between 25 and 75% of vital capacity (FEF 25–75) will be recorded in absolute values, as well as in percentages relative to gender, age and height. Up to three acceptable and two reproducible tests can be performed, and the highest value curve is recorded [44]. The values obtained in this study will be compared to the reference values proposed by Mallozi [45].

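### One of the five exacerbation criteria, a 10% fall in lung function seen on X-ray, cannot be scored as written and conflicts with the protocol's own spirometry

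*Protocol article*

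**What the plan says.** The abstract of the protocol article states that "the secondary outcomes will include lung function, exercise tolerance, respiratory muscle strength, quality of life, and CF exacerbations". The section CF exacerbations gives the definition, attributed to a published source (reference 32): "the following Fuchs criteria adapted by the European Consensus Group will be used". Five items follow, separated by semicolons:

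1. altered sputum amount or colour
2. "increases in coughing, fatigue or lethargy"
3. loss of appetite or weight
4. "decrease in lung function of 10% or more as observed on X-ray"
5. worse breathlessness

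The decision rule is: "The individual must present at least two of these criteria for an exacerbation to be confirmed".

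The section Lung function says how that quantity is measured in this trial: "Spirometry will be conducted using a KoKo DigiDoser spirometer". It records FVC, FEV1, their ratio and FEF 25–75. On timing, the abstract says "All outcomes will be assessed at baseline, week 9, and week 17".

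**The concern.** Item 4 joins a functional threshold to an imaging method that cannot deliver it. A chest film may show new changes, but it does not show that lung function has fallen by a tenth. None of the assessments described in the article is an X-ray. The schedule figure is not reproduced in the text at hand, but even a scheduled X-ray would not give this percentage.

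The item matters because the outcome is a count with a threshold of two. An assessor who follows the text scores item 4 as never met. One who assumes spirometry was meant scores it from the spirometer, and one who assumes two ideas were run together may accept either sign. Each can claim to be following the protocol, and they will not always agree on who had an exacerbation. Item 4 is also a measurement that the blinded assessor could make, whereas much of the remaining list depends on what unmasked families report.

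**Working it through.** The plan gives no figure for exacerbations. Its only computed figure, 20 participants for the glucose outcome, does not enter here. The check is a logical one on the definition.

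**Step 1: the two sections side by side.** CF exacerbations needs a fall of 10% or more in lung function and names X-ray as the means of seeing it. Lung function names a spirometer as the instrument. Both cannot describe the same measurement, and only the second produces a percentage. Neither the quantity that must fall nor the comparator is named in item 4.

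**Step 2: what the count does under each reading.** Take seven signs, each present or absent: sputum change, cough, fatigue or lethargy, appetite or weight loss, a spirometric fall of 10% or more, X-ray change, and breathlessness. That gives 2^7 = 128 patterns. A pattern is confirmed when at least two items are met, so confirmed = all patterns − patterns meeting no item − patterns meeting exactly one.

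Where cough and fatigue form one item, that item alone is met in 3 ways (cough, fatigue, or both).

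| Reading of the list | Arithmetic | Confirmed of 128 | More than literal |
|---|---|---|---|
| Literal: item 4 never met | 4 × (32 − 1 − 6) | 100 | – |
| Item 4 is a spirometric fall | 2 × (64 − 1 − 7) | 112 | 12 |
| Item 4 is a spirometric fall or X-ray change | 128 − 1 − 9 | 118 | 18 |
| Item 4 spirometric; cough and fatigue separate | 2 × (64 − 1 − 6) | 114 | 14 |
| All seven signs separate | 128 − 1 − 7 | 120 | 20 |

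The multipliers 4 and 2 cover signs that do not affect the count under that reading. The 12 extra patterns in the second row are those with a spirometric fall plus exactly one other listed item (6 patterns, with or without X-ray change). With item 4 spirometric, splitting cough from fatigue adds only 114 − 112 = 2.

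**Step 3: direction.** Every alternative keeps all that the literal reading can count and adds to it. The literal reading can therefore miss cases relative to the others but never add any.

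**Step 4: illustration of size.** The documents give no sign frequencies. Assume seven independent signs with the same prevalence p. The confirmed share is then:

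- literal: 1 − (1−p)^5 − 3p(1−p)^4 − [1−(1−p)^2](1−p)^3
- item 4 spirometric: 1 − (1−p)^6 − 4p(1−p)^5 − [1−(1−p)^2](1−p)^4
- all signs separate: 1 − (1−p)^7 − 7p(1−p)^6

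At p = 0.2 the literal share is 1 − 0.328 − 0.246 − 0.184 = 0.242, and the spirometric share is 1 − 0.262 − 0.262 − 0.147 = 0.328 (the terms are rounded).

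| p | Literal | Item 4 spirometric | All separate |
|---|---|---|---|
| 0.1 | 0.074 | 0.108 | 0.150 |
| 0.2 | 0.242 | 0.328 | 0.423 |
| 0.3 | 0.441 | 0.558 | 0.671 |

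Real signs of an exacerbation are correlated, so these shares show only that the choice of reading can matter. They do not predict this trial.

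**The case against.** The strongest reply is that the criteria are published, the protocol says they will be used, and the faulty phrase may be a slip in a condensed article. The full protocol and case report form may have it right, and assessors may simply use the spirometer. That is possible, and it limits the claim: the text shows a rule that can misclassify, not one that has. It does not remove the point, because this is a misstatement in the current definition and not a detail left to another document.

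Several stronger readings are tempting, and the documents do not support them.

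- **Cough and fatigue are wrongly merged.** The list groups related signs in other items too (amount and colour of sputum, appetite and weight). Whether this grouping is faithful depends on reference 32, which is not at hand. Only a request to state the counting rule is justified.
- **The only objective item is lost.** Weight loss is listed and can be measured, and the Anthropometry section describes a scale. That section belongs to sample characterization, however, and does not say that weighing is repeated.
- **The exclusion for exacerbation with hospitalization is affected.** It cites the same source but also requires admission. Nothing shows that the wording of item 4 would change who is excluded.
- **Rates shift by 10 percentage points.** With 10 children per arm, one reclassified child is 1/10 of an arm. Nothing says how many children, if any, would be reclassified.

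**Conclusion.** The definition is wrong as written on one item, for a secondary outcome only. Item 4 cannot be scored and contradicts the protocol's own method of measuring lung function. Because two criteria make a case, a literal reading can under-count exacerbations, and the classification is not reproducible between readers. In logical terms the literal reading confirms 12 to 20 fewer of 128 patterns than the alternatives considered. The effect on actual rates is unknown.

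The conclusion rests on the list being read as five items at its semicolons and on the count being applied as stated. That a functional item and a radiographic item were run together is a plausible explanation, but it is inference. The primary glucose outcome and the sample size of 20 do not depend on this.

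**What to change.** Reconcile the CF exacerbations section with the Lung function section and with reference 32:

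- Score the 10% fall from the trial's spirometry, naming the measure and the comparator as the source has them.
- List radiographic change as a separate item only if the source does.
- State whether cough and fatigue or lethargy count as one item or two, again following the source. Splitting items while keeping the threshold at two loosens the case definition (112 patterns become 120 with everything split), so it should not be done merely for tidiness.
- Apply the same rule in both arms, and carry the wording into the case report form.

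The cost is mainly a text correction, since spirometry is already performed. There are two drawbacks. Recruitment was under way when the article was submitted, so children already assessed need re-scoring under the corrected rule. The spirometric item can also be scored only where spirometry exists: at baseline, week 9 and week 17, or from routine care. The protocol should say how the item is handled for an exacerbation that falls between visits with no spirometry.

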### Patient safety

Adverse events will be monitored in both arms of the trial. Any adverse events that are thought to be causally associated with the intervention will be recorded, managed, and reported to the study coordinators. Serious adverse reactions will be reported to the ethical committee. The study coordinators will compensate participants who experience adverse effects related to the intervention.

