### Experimental group (EG)

The EG will receive an educational intervention similar to the one conducted with CG, with additional instructions on how to perform the experimental training. The AIT program will be conducted at home, three times a week on alternating days, and using a cycle ergometer for lower limbs (Altmayer Sport). Each session will start with 5 min of warm-up and end with 5 min of cool-down at 30 to 40% of the maximum heart rate (MHR). The training in the initial two weeks will be carried out in six bouts of 20 s, reaching between 70 and 80% of MHR, interspersed by 2 min of active rest, and reaching between 50 and 60% of MHR [33, 39]. Progression will be carried out every 2 weeks by adjusting the time and the amount of the bouts as shown in Table 1.

**Table 1 Tab1:** Progression of high-intensity interval training protocol for children and adolescents with CF

Week	Warm up	Bout	est	Cool down	Training time	Total time
1	5 min	6 sprints / 20 s	2 min	5 min	14 min	24 min
2	5 min	6 sprints / 20 s	2 min	5 min	14 min	24 min
3	5 min	8 sprints / 20 s	2 min	5 min	18 min 40 s	28 min 40 s
4	5 min	8 sprints / 20 s	2 min	5 min	18 min 40 s	28 min 40 s
5	5 min	8 sprints / 30 s	2 min	5 min	20 min	30 min
6	5 min	8 sprints / 30 s	2 min	5 min	20 min	30 min
7	5 min	10 sprints / 30 s	2 min	5 min	25 min	35 min
8	5 min	10 sprints / 30 s	2 min	5 min	25 min	35 min

Participants will be instructed to hydrate with a quantity of water equivalent to or greater than 500 ml during the training [40]. The intensity of the exercises will be monitored by the frequency meter (Beurer PM15).

Participants will be given a diary before the treatment to record information about the disease exacerbation, heart rate, and the modified Borg scale, as well as to record signs and symptoms observed during training. They will also be shown how to use the diary (Additional file 3). The information will be recorded by the parents and/or caregivers before and after each treatment day. The diary with all the registered information will be returned to the researcher after completion of the treatment for use in evaluating adherence to the proposed intervention. Researcher 4 will maintain weekly contact via cell phone with the parent/guardian to stimulate the intervention and minimize possible deviations from the protocol.

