## Discussion

CFRD is preceded by and associated with delayed weight development and loss of lung function, which increase the mortality risks in these individuals [9, 10]. Current treatment uses insulin, but no consensus exists on the treatment of glucose intolerance [33]. Evidence exists that interval exercise promotes reduced plasma glucose [55] and increased insulin sensitivity [56] in individuals with T2DM and in adults with CF [21]. This is the first study to evaluate the effects of AIT on glucose tolerance, function, exercise tolerance, respiratory muscle strength, quality of life, and CF exacerbations in children and adolescents with CF.

This study presents some strengths not present in previous studies, such as the utilization of AIT as an intervention for CF children and adolescents, glucose tolerance outcome, and appropriate assessment instruments. Moreover, this study can be considered of high methodological quality because it is randomized; prospectively recorded; and uses masked evaluators, concealed allocation, and an intention-to-treat approach. If AIT increases the glucose tolerance, it could represent an effective and safe treatment for these individuals. This study will serve as a basis for guiding clinical practice and decision-making in treating glucose intolerance and CFRD in children and adolescents with CF.

A limitation of the study relates to performing the AIT at home without professional supervision. The lack of a professional to supervise the training sessions does not guarantee correct execution of the protocol nor that the training heart rate is reached. However, home exercises more closely reproduce the reality for these children and adolescents, thus enabling identification of reproducible results in any place and promoting the self-management of CF.

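### Adverse events are recorded only if attributed to the intervention, so the arms cannot be compared on all adverse events; exacerbation capture is also at risk of differing between arms

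*Protocol article*

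**What the plan says.** **Adverse events.** The Patient safety section opens with a two-arm commitment: "Adverse events will be monitored in both arms of the trial". The next sentence sets the recording rule: "Any adverse events that are thought to be causally associated with the intervention will be recorded". Onward reporting is also limited to attributed events: "Serious adverse reactions will be reported to the ethical committee". The section does not say who judges causality.

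**Safety claim.** The Discussion says that, if glucose tolerance improves, the training is something of which "it could represent an effective and safe treatment for these individuals".

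**Diary and calls.** The Experimental group (EG) section provides a diary: "Participants will be given a diary before the treatment to record information about the disease exacerbation, heart rate, and the modified Borg scale". It also covers signs and symptoms seen during training. Parents fill it in around each training day and hand it back when treatment ends, and its stated use is to judge adherence. The same section adds: "Researcher 4 will maintain weekly contact via cell phone with the parent/guardian". The stated aim of the calls is to encourage training and limit deviations. The Control group (CG) section describes one 20-minute educational session in week 1 and a booklet, and mentions neither a diary nor calls.

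**Exacerbation outcome.** CF exacerbation is a secondary outcome. It is defined for everyone by at least two criteria from a list made up mostly of symptoms. The Abstract and the Intervention section give both arms the same assessments at baseline and in weeks 9 and 17. The Masking/blinding section keeps the assessor blind to group, and the Data management section has that assessor obtain the data from the child and the parent or guardian.

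**The concern.** The two opening sentences of the Patient safety section pull against each other. Watching both arms is useful for comparison only if what is seen in both arms is written down. A filter on attribution to the intervention passes some training-arm events and almost no control events. Attributing an event to training also requires knowing that the child trained, so the filter cannot be applied blind to allocation, whoever applies it.

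Two errors become possible. Ordinary background events in the training arm may be put down to exercise while the same events in controls go unrecorded, which makes training look worse than it is. Conversely, a real excess of a kind nobody links to exercise would be dropped, and no comparison of arms could reveal it. The participants are children and adolescents with CF who train at home, and the Discussion itself lists the lack of professional supervision as a limitation.

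The exacerbation outcome has a related but weaker problem. One group of families keeps notes about exacerbations and is phoned weekly for eight weeks. No equivalent is described for the other. If this changes what families notice or remember, the arms could differ in reported exacerbations without differing in true ones.

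**Working it through.** The plan gives no figure for safety or exacerbations, so there is nothing to reproduce. The only design figure used is 10 participants per arm (Sample size calculation). All other inputs below are assumptions, shown as ranges.

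**1. The recording rule, read literally**
- Training-arm event, attributed to training: recorded.
- Training-arm event, not attributed: no requirement to record it as an adverse event.
- Control event: the child did no training, so attribution to it is not possible. The control section does call its educational session an intervention, but few events could plausibly be caused by a presentation and a booklet.

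The recorded events therefore estimate the number of attributed events in the training arm. They do not estimate a difference between arms.

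**2. Illustration for adverse events**

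Expected recorded events = n × b × a, where n = 10 per arm, b is the background risk (assumed equal in both arms, 0.20 to 0.40), and a is the probability of attribution (assumed 0.25 to 0.75 with training, 0 in controls).
- True expected events in each arm: 10 × 0.20 = 2 to 10 × 0.40 = 4.
- Recorded, training arm, lowest: 10 × 0.20 × 0.25 = 0.5.
- Recorded, training arm, highest: 10 × 0.40 × 0.75 = 3.0.
- Recorded, control arm: 10 × b × 0 = 0.

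Equal true risks thus give 0.5 to 3.0 events against none. For a type of event that nobody attributes to training, a = 0 in both arms and the record reads 0 against 0, however large the true excess.

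**3. Exacerbations: what the sections establish**
- The diary and calls appear only under the experimental group. The diary is tied to training days, which controls do not have, and neither item is in the Intervention section that sets out what both groups share.
- The definition, the visits and the blinded assessor are common to both arms.
- No section says that the diary or the calls feed the exacerbation outcome, and none names a source for exacerbations between visits in either arm.
- The diary is returned at the end of treatment, so the described asymmetry covers the eight training weeks and not the later follow-up.

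**4. Illustration for exacerbations**

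With equal true risk, apparent risk ratio = detection in the training arm ÷ detection in controls. Assume complete detection in the training arm and a true risk of 30%, so that 10 × 0.30 = 3.0 training-arm cases are expected.

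| Control detection | Apparent risk ratio | Expected cases, training v control | Chance that Fisher's test gives P < 0.05 |
|---|---|---|---|
| 50% | 1/0.5 = 2.00 | 3.0 v 1.5 | 0.034 |
| 70% | 1/0.7 = 1.43 | 3.0 v 2.1 | 0.019 |
| 90% | 1/0.9 = 1.11 | 3.0 v 2.7 | 0.012 |
| 100% | 1.00 | 3.0 v 3.0 | 0.012 |

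Unequal detection would distort the estimate but would rarely produce a significant difference at this sample size. Under these assumptions it works against the training arm, so it could hide a benefit but would not create one. The documents give no basis for choosing a row.

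**The case against.** **On adverse events.** The section does promise monitoring in both arms, and the training diary notes signs and symptoms with no attribution test, so unattributed events need not vanish altogether. Safety is not a listed outcome, and the Discussion sentence is conditional, not a planned analysis. These points are fair, but they do not rescue the comparison. Monitoring without recording leaves nothing to analyse, and the diary has no described counterpart in controls. Nor can the rule be put down to the condensed form of an article, because it is stated explicitly.

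**On exacerbations.** Here the other side is stronger. A reader might infer that exacerbations are captured by diary in one arm and by recall in the other, so that they will be over-counted with training and cannot be compared without bias. The documents do not support this. They give the diary and calls other purposes, link neither to the outcome, and provide one definition and common blinded visits. Some criteria, such as lung function and weight, can be measured. The control side rests on placement and silence in a condensed article. What remains is a risk: most criteria are symptoms reported by families who know their allocation, and a blinded assessor cannot equalise what those families noticed or wrote down.

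**On remedies.** Weekly calls to controls would change the comparator, because the calls are part of the support given with training. That would be a trade-off, so the fix does not require it.

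**Conclusion.** The adverse-event point stands. As written, the rule rules out any comparison of all-cause adverse events between arms, and a statement that training is safe relative to control would have no comparative data behind it. This conclusion needs no numerical assumption. It follows from the recording rule and from the absence of training in the control arm. The 0.5 to 3.0 against 0 figures only illustrate it.

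The exacerbation point stands only as a risk of differential ascertainment, of unknown size. It rests on the diary and calls being confined to the training arm, as their placement suggests, and on their influencing what families report at the shared visits. The apparent risk ratios of 1.11 to 2.00 depend wholly on assumed detection rates and are not estimates for this trial.

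Neither point touches the primary glucose outcome. Both are worth correcting in the protocol, because events that were never recorded may not be recoverable at analysis.

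**What to change.** 1. **Recording rule.** In the Patient safety section, require every adverse event in both arms to be recorded, whatever its suspected cause. Enter seriousness and causality as separate fields, and report events by arm regardless of attribution, with attributed events as a further breakdown.
2. **Same contacts.** Ask about adverse events in the same way in both arms at the week 9 and week 17 visits. Flag anything first learned through the training diary or the calls, so that it can be set apart in the comparison. Causality should be assigned by someone other than the blinded assessor, because that judgement requires knowing the allocation.
3. **Exacerbations.** Choose one of two routes and state it. Either give both arms the same symptom checklist or diary pages, without the training pages for controls, on the same schedule; or state that the outcome rests only on the blinded visits in weeks 9 and 17 and not on the training diary or calls.
4. **Transition.** Recruitment was already under way when the article was submitted, so give the date of the change and show events recorded before and after it separately.

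The cost is some extra recording for the 10 controls and, on the first route, ten sets of pages. No extra visits are needed.
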